#### Patient recruitment

Eligible patients are those aged 18 and over presenting to their GPs who are daily or weekly smokers. Potential participants will be excluded if they meet any of the following criteria: unable to give informed consent (poor physical and/or cognitive state), insufficient command of English to comprehend the consent process and/or data collection questions. A research assistant will be attached to each participating practice for a two week recruitment period and approach patients in the waiting room prior to the consultation with the GP. Initially the research assistant will assess patient eligibility and, if eligible, patients will be given a copy of participant information statement. Patients providing a written consent will be asked to complete the baseline data questionnaire at this time. Patients take notice of their participation into the GP consultation. GPs respond to this notification depending on their group allocation.

This method of recruitment maintains a separation of baseline data collection from the intervention. Waiting room recruitment has previously been used successfully by members of the research team in studies on smokers, [37,38] risky drinkers [39] and overweight and obese patients [40].

### Intervention

#### Quit with Practice Nurse

This intervention involves the practice nurse, GP and Quitline working in partnership with the patient to provide flexible assistance that meets the needs of individual smokers. The GP identifies smokers and their willingness to quit and offers brief advice. Patients with any interest in quitting are referred to the practice nurse. The practice nurses will see the patient for an initial assessment visit. At this assessment the practice nurse gathers information about patient demographics, smoking behaviour, stage of readiness to quit, previous quit attempts, nicotine dependence (using Fagerstrom test), previous use of pharmacotherapy and perceived barriers to quitting. Patients are assisted to develop a quit plan and (in consultation with the GP) encouraged to use pharmacotherapy according to recommendations in clinical practice guidelines [11,41]. Patients are then offered a flexible package of ongoing support. Those able to attend for face-to-face counseling are offered a series of weekly (three follow-up visits) visits with the practice nurse. At these visits patients are provided behavioural counseling, support in use of pharmacotherapy, relapse prevention advice and encouragement of social support as shown in table 1.

**Table 1 T1:** Practice Nurse Visits

	Visit 1	Visit 2	Visit 3	Visit 4
Smoking assessment	✓			

Nicotine dependence assessment	✓			

Pharmacotherapy discussed	✓	✓	✓	✓

Nicotine patches offered to eligible patients	✓		✓	✓

Quit support plan developed	✓			

Cessation counseling support	✓	✓	✓	✓

Patients in this group who are unable to attend for face-to-face consultations or who prefer telephone counseling to support their quit attempts will be referred to the Quitline using a faxed referral system. As in the referral intervention described below, patients are contacted and offered services to meet their needs. Patients are encouraged to use the proactive callback service which has been shown to be more effective than reactive counseling [42]. Feedback is provided by the Quitline to the practice on acceptance, use and outcomes of services offered to facilitate the ongoing management of the patient in the practice. Patients who are able to attend one or two practice nurse visits will be offered a combination of nurse counseling and referral to Quitline.

#### Nurse training for 'Quit with Practice Nurse' intervention

Training for the practice nurses will consist of a one day training workshop where the nurses are educated in: 5As approach to smoking cessation counseling (Ask, Assess, Advise, Assist, Arrange follow-up); basics of motivational interviewing; nicotine dependence; smoking cessation pharmacotherapy and resources for smoking cessation including Quitline services. The practice nurses will receive mentoring over the course of the project from an experienced Quitline counselor who they can contact for advice. The counselors involved will attend the practice nurse training sessions to establish this mentoring relationship

#### Active referral to Quitline

The '**Quitline Referral' **intervention involves the GPs identifying smokers and their willingness to quit and offering brief advice. Patients with any interest in quitting are offered referral to the Quitline. Patients who consent will have their referral faxed to the Quitline and are provided with a brochure on Quitline services. Patients are telephoned by the Quitline and offered services to meet their needs. Patients who express interest in quitting are offered a series of proactive callback counseling/advice sessions [42]. Referring practices are provided with feedback from the Quitline on acceptance, use and outcomes of services offered to facilitate ongoing management of the patient. GPs are expected to provide advice on use of medications and prescriptions where appropriate.

#### Control Group

The control group involves GPs identifying smokers and their willingness to quit and offering assistance in accordance with their usual practice. This should include advice on use of medications to quit and prescriptions where appropriate. It may involve advice provided by themselves within the practice or referral to the Quitline or both where the GP deems it appropriate, but no provision is made to facilitate either. Based on previous work, levels of either referral or intense counseling within practice interventions are likely to be very low [16].

#### Smoking cessation pharmacotherapy

Patients in all three groups will be encouraged to use smoking cessation pharmacotherapy based on best practice guidelines [11,41]. For patients in all three groups who are on low incomes and therefore eligible for subsidised medicines under the Australian Government Pharmaceutical Benefit Scheme (PBS) the project will fund access to nicotine patches. This targeted subsidy will not disrupt the ecological validity of the study as a test of the different modes of cessation support as it will be offered equally across all three arms of the study

#### Outcome measures

Patient level measures will be assessed at baseline, three months and 12 months (the schedule of data collection is shown in table 2. At baseline patients will be asked to complete a paper questionnaire assessing demographics including age, sex, language spoken at home, ethnicity, education levels, occupation, current level of smoking, nicotine dependence, quitting history and presence of co-morbidities. Three month and 12 month data will be collected by Computer Assisted Telephone Interview (CATI) by trained interviewers who are blind to intervention group until after the outcome data is collected.

**Table 2 T2:** Schedule of data collection

	At recruitment	3-months	12-months
Age, gender, language spoken at home,	X		
Smoking history	X	X	X
Nicotine dependence	X	X	X
Sustained abstinence		X	X
Point prevalence abstinence		X	X
Quit attempts			X
Intervention costs		X	X
Process evaluation data from patients			
Process evaluation data from PN, GPs and Quitline counselors			X

#### Primary outcomes

Uptake of the intervention in each group and characteristics of patients - age, sex, language spoken at home, ethnicity, education levels, occupation, smoking history, level of smoking and nicotine dependence.

Smoking cessation rates: sustained abstinence defined as patients reporting abstinence of ≥ one month at the three month follow-up and ≥ 10 months at the 12 month follow-up; and point prevalence abstinence defined as ≥ seven days of sustained abstinence at the three month and 12 month follow-up points. Validation of smoking cessation will not be undertaken as reviews confirm the accuracy of self-report measures, and conclude that validation is unnecessary in trials where there is no strong association between the interviewer and respondent [43]. Number and duration of quit attempts will be a further outcome measure as it is known that the key effect of advice from a health professional is to encourage the smoker to try to quit [10,11].

Health economic outcomes: the economic evaluation will compare the flexible support intervention 'Quit with Practice Nurse' and the 'Quitline referral intervention' with standard 'in practice management by the GP' (control group.) Cost analysis will be from the perspective of the health care sector and include direct costs of the intervention, including for recruitment, and for the intervention (GP costs, practice nurse costs, nurse training costs, telephone counseling costs, pharmaceutical costs, and overheads such as room rents).

#### Process outcomes

Quantitative and qualitative data on process outcomes will be collected as part of the CATI of participating patients in each of the three arms at the three month follow-up point. These questions will be asked only after the primary outcome data on abstinence has been collected. In the CATI patients in all three arms will be asked about uptake including barriers and enablers to uptake, extent and nature of the intervention received including use of smoking cessation pharmacotherapy (type of pharmacotherapy used and duration of use), acceptability and perceived value of the smoking cessation support received. The interviews will also explore patient perception on the influence of culture, language and socioeconomic status on the acceptability of the intervention approaches. Patients in the 'Quit with Practice Nurse' arm will be asked further questions about the perceived value of the flexible approach to cessation support. These will include their level of awareness or lack of awareness of the flexibility, its importance or otherwise for them, the important factors in the choices made about support options, and their perception on the roles of the providers involved (practice nurse, GP and Quitline counselor).

The acceptability and sustainability of the 'Quit with Practice Nurse' intervention will be evaluated with semi-structured interviews with participating practice nurses, GPs and Quitline counselors.

#### Data Analysis

Analysis for the primary outcomes of sustained abstinence and point prevalence abstinence will be on an intention to treat basis with cases retained regardless of whether they accept or receive the intended intervention. A series of planned imputation strategies for missing data will be used in examining outcomes for missing data. These are 1) analysis will be done on all participating patients, where all patients with missing outcome data will be assumed to be smokers; 2) the last known value carried forward to replace the missing value; 3) an analysis of outcomes for patients with complete outcome data. We will compare cessation outcomes between the three arms at three months and 12 month follow-up using multiple logistic regression. This approach will allow us to adjust for clustering and to assess the effect of potential confounders such as age, sex, socioeconomic status, ethnicity, language spoken at home and nicotine dependence on cessation outcomes.

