**Methods/Design:**

This study is a cluster randomised trial, with practices allocated to one of three groups 1) Quit with Practice Nurse 2) Quitline referral 3) GP usual care. PNs from practices randomised to the intervention group will receive a training course in smoking cessation followed by access to mentoring. GPs from practices randomised to the Quitline referral group will receive information about the study and the process of written referral and GPs in the usual care group will receive information about the study. Eligible patients are those aged 18 and over presenting to their GP who are daily or weekly smokers and who are able to give informed consent. Patients on low incomes in all three groups will be able to access free nicotine patches.

Primary outcomes are sustained abstinence and point prevalence abstinence at the three month and 12 month follow-up points; and incremental cost effectiveness ratios at 12 months. Process evaluation on the reach and acceptability of the intervention approached will be collected through Computer Assisted Telephone Interviews (CATI) with patients and semi-structured interviews with PNs and GPs.

The primary analysis will be by intention to treat. Cessation outcomes will be compared between the three arms at three months and 12 month follow-up using multiple logistic regression. The incremental cost effectiveness ratios will be estimated for the 12 month quit rate for the intervention groups compared to usual care and to each other. Analysis of qualitative data on process outcomes will be based on thematic analysis.

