### Quitline referral

An alternative to in-practice support from the GP is for GPs to identify smokers, provide brief advice and actively refer interested patients to the telephone Quitline. A study in Australia which compared standard in-practice management to this active referral to Quitline has shown that at 3 month follow up patients randomised to the referral intervention had a higher rate of sustained abstinence (12.3% compared with 6.9%). At 12 month follow-up patients in the referral intervention had a higher rate of sustained abstinence (6.5% compared to 2.6%), however this did not reach statistical significance [16]. The researchers concluded that GPs referring smokers to an evidence based telephone cessation service can result in increased cessation.

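### Carrying the last value forward is invalid for 12-month sustained abstinence, because 3-month status cannot establish ten months without smoking

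*Protocol article*

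**What the plan says.** - **Endpoint.** Under Primary outcomes, sustained abstinence is "abstinence of ≥ one month at the three month follow-up and ≥ 10 months at the 12 month follow-up". Point prevalence abstinence uses one definition, at least seven days, at both visits.
- **Missing data.** Data Analysis, which covers both abstinence outcomes, says: "A series of planned imputation strategies for missing data will be used in examining outcomes for missing data". The three are (1) "all patients with missing outcome data will be assumed to be smokers", on all participating patients; (2) "the last known value carried forward to replace the missing value"; and (3) "an analysis of outcomes for patients with complete outcome data". No outcome or time point is exempted from (2).
- **Visits.** Outcome measures schedules follow-up at 3 and 12 months only.
- **Analysis basis.** The abstract states: "The primary analysis will be by intention to treat". Data Analysis specifies logistic regression.
- **Powered endpoint.** Sample size uses 12-month sustained abstinence: 2.6% usual care, 6.5% referral, 12% nurse support.

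**The concern.** The same name covers two different measurements. A patient who reports one month of abstinence at month 3 and is then lost would be scored, under strategy 2, as abstinent for at least 10 months at month 12. Nobody has observed the nine months in between.

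The error runs one way. Ten months of abstinence at month 12 means having stopped by about month 2. A patient still smoking at month 3 is therefore correctly carried forward as a failure, while a patient abstinent at month 3 is carried forward as a success whether or not relapse follows. The rule can only raise the rate.

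The protocol itself expects relapse. Sample size assumes that the nurse arm falls from 16% at six months to 12% at 12 months, and Health economic analysis allows for relapse even after month 12. Loss is also foreseeable: the Background section reports poor retention of smokers in earlier practice nurse studies. At stake are the 12-month quit rates under this strategy, and the cost per quitter if it were fed from them.

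**Working it through.** **1. The plan's own figure.** Two-sided 5% level, 80% power, two proportions with continuity correction: 6.5% v 12% gives 471 per group, and 2.6% v 12% gives 140. Design effect 1 + 24 × 0.013 = 1.312, rounded to 1.31; 471 × 1.31 = 617; 3 × 617 = 1851. All agree with the Sample size section. These figures are not in dispute; they confirm that 12-month sustained abstinence is the powered endpoint.

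**2. Inputs.** From the Quitline referral section (cited study), sustained abstinence at 3 months (p3) and 12 months (p12):
- referral: 12.3% and 6.5%, ratio 6.5/12.3 = 53%;
- usual care: 6.9% and 2.6%, ratio 2.6/6.9 = 38%.

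Carry-forward treats this ratio as 100% among those lost.

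**3. Formula.** Let m be the fraction of an arm seen at month 3 but missing at month 12. The protocol gives only a practice drop-out of about 10%, so m is an assumption. If those lost share the cited rates:
- rate under carry-forward = (1 − m) × p12 + m × p3;
- overstatement = m × (p3 − p12), which is 5.8m points for referral and 4.3m for usual care.

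| m, both arms | Referral (excess) | Usual care (excess) | Risk difference | Odds ratio |
|---|---|---|---|---|
| 0 | 6.5% | 2.6% | 3.9 | 2.60 |
| 10% | 7.08% (0.58) | 3.03% (0.43) | 4.05 | 2.44 |
| 20% | 7.66% (1.16) | 3.46% (0.86) | 4.20 | 2.31 |
| 30% | 8.24% (1.74) | 3.89% (1.29) | 4.35 | 2.22 |

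The odds ratios follow from the rates. For example, (6.5/93.5)/(2.6/97.4) = 2.60 and (7.66/92.34)/(3.46/96.54) = 2.31.

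**4. Unequal loss.** With 20% lost in usual care and 30% in referral, the difference is 8.24 − 3.46 = 4.78 points. With 30% and 20%, it is 7.66 − 3.89 = 3.77, below the true 3.9.

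**5. Nurse arm.** The protocol gives no 3-month rate. Assuming p3 from 16% to 25% and m = 20%, the overstatement is 0.2 × (16 − 12) = 0.8 to 0.2 × (25 − 12) = 2.6 points. Nurse minus referral becomes 12.8 − 7.66 = 5.14 to 14.6 − 7.66 = 6.94, against the planned 5.5.

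**6. Bounds.**
- Patients already missing at month 3 carry forward baseline smoking and add no inflation. If they make up half of a 20% loss, the excess halves to 0.58 and 0.43.
- If everyone lost after month 3 had in fact relapsed, the excess is m × p3: at 20%, 2.46 points (referral) and 1.38 (usual care).

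**The case against.** Four arguments weigh against making much of this.

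- **Carry-forward is one of three planned strategies.** It is listed second, and the text commits to running all three, so disagreement would be visible. Missing = smoker comes first, covers all participants and best fits intention to treat. This stands. A reader might infer that the headline result can be picked afterwards because no strategy is called primary. The document does not support that: the strategies are fixed in advance, and naming the primary one is commonly left to an analysis plan that is not shown.
- **The comparison is hardly inflated.** This stands. On the cited rates with equal loss, the odds ratio, which is the scale of the planned regression, falls.
- **The cited fall may not all be relapse.** The protocol does not give that study's definitions or its handling of missing data. If loss was counted as smoking there, part of the fall is loss. This stands as a limit on the size, not on the mismatch of definitions.
- **Point prevalence is different.** Its seven-day definition is the same at both visits, so the mismatch does not arise, and removing strategy 2 altogether would go too far. This stands.

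A reader might also infer that the rule would make a purely early effect look like a 12-month effect. Suppose both arms truly had 6.5% at month 12, but 12.3% v 6.9% at month 3. At m = 20%, carry-forward gives 7.66% v 0.8 × 6.5 + 0.2 × 6.9 = 6.58%, a spurious gap of 1.08 points. But that needs a 12-month to 3-month ratio of 6.5/6.9 = 94% in the comparison arm, against the cited 38% for usual care. The protocol's figures do not support that case.

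None of this makes the carried value a valid reading of 12-month sustained abstinence.

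**Conclusion.** The point holds for one strategy applied to one endpoint. Applied as written, strategy 2 scores unobserved patients as meeting a definition that their last value cannot establish, and each arm's 12-month sustained rate is biased upwards. With 10% to 30% lost after month 3, the excess is 0.58 to 1.74 points in referral and 0.43 to 1.29 in usual care. Set against rates of 6.5% and 2.6%, that is not trivial.

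The consequence for the comparison is modest and its direction is not fixed. At 20% equal loss the risk difference widens by 0.3 points while the odds ratio shrinks from 2.60 to 2.31, and unequal loss can move the difference either way. It should not be read as a built-in advantage for the nurse arm.

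The sizes rest on an assumed loss and on those lost sharing the cited study's rates. The mismatch of definitions rests on neither.

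**What to change.** In Data Analysis, state that:

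- 3-month status is not carried forward into 12-month sustained abstinence, and only a report of at least 10 months at the 12-month interview counts as success;
- missing = smoker (strategy 1) is the main analysis for this endpoint;
- complete cases (strategy 3) is a sensitivity analysis, with multiple imputation using 3-month status as an optional further one.

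Missing = smoker has its own bias, towards lower rates. At 20% missing it gives 0.8 × 6.5 = 5.20% and 0.8 × 2.6 = 2.08%, a difference of 3.12 points instead of 3.9, which is why the sensitivity analyses should stay. Strategy 2 may remain for point prevalence, where the definition does not change.

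The cost is wording and minor programming, with no new data. The change should be made before outcomes are analysed by arm.

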#### Health economic analysis

The study will estimate incremental cost effectiveness ratios (ICER) of cost per quitter for brief advice and referral to Quitline, and with the flexible support intervention, compared to standard GP care. The ICER will be estimated for the 12 month quit rate for the intervention, less an unaided/natural quit rate. Adjustments to effect sizes will also be made for long term relapse rate among the 12 month quitters.

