### Cost effectiveness of smoking cessation interventions

Smoking cessation strategies have been shown to be highly cost effective compared to many pharmacological, surgical and hospital treatments or services [33]. A recent systematic review of studies in a range of settings adjusted for variation in program effects and costing methods found cost effectiveness ratios ranged from US$490 to $US15280 per life-years saved (LYS) in different settings [34].

Face to face interventions are the most common strategies. A recent review of cost effectiveness studies for such face to face health behaviour interventions addressing smoking cessation found favourable cost effectiveness ratios for smoking cessation programs compared to preventative pharmaceutical and invasive interventions [35].

More intensive interventions may be more effective but also more costly [10]. Many studies omit disadvantaged populations which are known to have higher levels of smoking [10]. Health gains are likely to be larger in such groups. Hence it is proposed that although more intensive interventions may be more costly, cost effectiveness will still be very favourable as a result of the high health gains. The cost effectiveness analysis in this study will compare the more intensive interventions to usual care.

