### Specifically the study will

• Evaluate uptake of the 'Quit with Practice Nurse' intervention versus the referral intervention and the control group in terms of the number of patients, demographics, socio-economic status, language and ethnicity, smoking history and level of nicotine dependence. *Hypothesis: the 'Quit with Practice Nurse' intervention will reach more smokers because it will meet the needs of a greater range of smokers with different demographic, socioeconomic and cultural characteristics than referral model or standard in-practice GP management*.

• Compare the effect on cessation of 'Quit with Practice Nurse' versus 'Quitline Referral' and the control group. *Hypothesis: the 'Quit with Practice Nurse' model will achieve higher quit rates as more patients will receive a cessation intervention that meets their individual needs*.

• Examine the cost effectiveness of the three approaches and their components from the perspective of the health care sector. *Hypothesis: the more intensive intervention may be more costly than usual care or 'Quitline Referral' but any higher costs of the 'Quit with Practice Nurse' intervention will be justified by its higher uptake and quit rate*.

• Assess the acceptability to patients of the 'Quit with Practice Nurse' intervention. *Hypothesis: the 'Quit with Practice Nurse' intervention will be acceptable to patients as it offers a flexible package of support to meet patient needs*.

• Assess acceptability and sustainability of practice nurse assisted support to quit from the perspective of practice nurses and GPs. *Hypothesis: the 'Quit with Practice Nurse' intervention will be acceptable to practice nurses and GPs as it provides an important new role for practice nurses and provides GPs the option of referral within their practice*.

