#### Sample size

The observed 12 month sustained abstinence outcomes of GP usual care and Quitline referral in Borland et al.'s study in Victoria were 2.6% and 6.5% respectively [16]. The sustained abstinence at six months in a pilot study of practice nurse support was 16%. Assuming this drops to 12% at 12 months we have calculated power to detect a 5.5% difference in sustained abstinence quit rates between 'Quit with Practice Nurse' intervention versus the referral intervention and a 9.4% difference between 'Quit with Practice Nurse' intervention and the usual care control group at one year follow up with 80% power at the 5% significance level. Before adjustment for clustering this requires 471 patients per group to detect the 5.5% difference and 140 per group to detect the 9.4% difference (calculations using STATA software). To adjust for clustering the intracluster correlation coefficient observed by Lennox et al. in a smoking cessation trial in general practice has been used. The intracluster correlation coefficient observed in this study was 0.013 [45]. The resulting design effect = [1+ (size of cluster-1) × intracluster correlation]. In this study we plan to recruit 25 patients per practice so the design effect is 1.31 so the number per arm is 471 × 1.31 = 617 giving a total sample size of 1851. To enroll these participants we will recruit 90 general practices and 2250 patients across New South Wales and Victorian study locations (to allow for approximately 10% drop out rate of practices) and randomise 30 practices to each arm of the study.

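### The economic Methods compare each intervention only with usual care, while the abstract and the hypothesis also call for the nurse model against Quitline referral

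*Protocol article*

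**What the plan says.** Three places in the body of the protocol article name usual care as the only economic comparator:

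- Health economic analysis: "cost per quitter for brief advice and referral to Quitline, and with the flexible support intervention, compared to standard GP care".
- Primary outcomes section: "the economic evaluation will compare the flexible support intervention 'Quit with Practice Nurse' and the 'Quitline referral intervention' with standard 'in practice management by the" (the sentence ends by identifying this comparator as the control group).
- Background, Cost effectiveness of smoking cessation interventions: "The cost effectiveness analysis in this study will compare the more intensive interventions to usual care".

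Two places go further:

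- Abstract, Methods/Design: the ICERs are to be estimated "for the intervention groups compared to usual care and to each other".
- Specifically the study will: the objective is to "Examine the cost effectiveness of the three approaches and their components from the perspective of the health care sector". The hypothesis is that "the more intensive intervention may be more costly than usual care or 'Quitline Referral' but any higher costs of the 'Quit with Practice Nurse' intervention" are worth paying because uptake and quitting will be higher.

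The abstract lists the 12-month ICERs among the primary outcomes, and the body places health economics under the same heading.

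**The concern.** The three arms are mutually exclusive ways of supporting the same smoker. A ratio against the least effective arm does not show whether moving from Quitline referral to the nurse model is worth its added cost. That needs the increment between those two arms. The Aims and objectives section presents referral as the main competing model and counts the comparison with both referral and usual care as a strength of the trial. The sample size is also set by nurse versus Quitline. Yet this is the comparison that the economic Methods leave out.

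Two things are at stake. The set of ICERs planned for a primary outcome depends on which section is read, so the choice could be made after the results are known. And the figure that the Methods do provide may lie well away from the one that the hypothesis needs.

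**Working it through.** **The plan's own figures.** The article states no cost and no ICER. Its only relevant numbers are in the Sample size section. The two-proportion formula with continuity correction (two-sided 5%, 80% power) gives 471 per group for 6.5% v 12% and 140 for 2.6% v 12%, as stated. The design effect is 1 + 24 × 0.013 = 1.312; 471 × 1.31 = 617 per arm; 617 × 3 = 1,851. These reproduce and are not in dispute. They confirm that nurse versus Quitline (471), not nurse versus usual care (140), sets the size of the trial.

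**Inputs.** The 12-month sustained abstinence rates for usual care (U) and Quitline referral (Q) are those the article reports from the earlier Australian trial ("in Victoria were 2.6% and 6.5% respectively"). The nurse model (N) is assumed there to reach 12%.

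- Q − U = 6.5 − 2.6 = 3.9 points
- N − U = 12 − 2.6 = 9.4 points
- N − Q = 12 − 6.5 = 5.5 points

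Let cQ and cN be the added cost per patient over usual care. They are not documented, so every value below is an assumption in arbitrary currency units.

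**Formulas.** Q v U = cQ / 0.039. N v U = cN / 0.094. N v Q = (cN − cQ) / 0.055.

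Hence N v U = (3.9/9.4) × (Q v U) + (5.5/9.4) × (N v Q). The usual-care ratio for the nurse model is a weighted average of the other two. It lies below N v Q exactly when cQ/3.9 < cN/9.4, that is, when cN/cQ > 9.4/3.9 = 2.41.

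| cQ, cN (assumed) | cN/cQ | Q v U | N v U | N v Q |
|---|---|---|---|---|
| 50, 300 | 6.0 | 1,282 | 3,191 | 4,545 |
| 50, 200 | 4.0 | 1,282 | 2,128 | 2,727 |
| 100, 300 | 3.0 | 2,564 | 3,191 | 3,636 |
| 100, 241 | 2.41 | 2,564 | 2,564 | 2,564 |
| 100, 200 | 2.0 | 2,564 | 2,128 | 1,818 |
| 100, 150 | 1.5 | 2,564 | 1,596 | 909 |

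In the last two rows Quitline's own ratio (2,564) exceeds the nurse model's ratio over Quitline. Quitline is then extendedly dominated, and nurse versus usual care becomes the relevant ratio. Which comparison matters therefore cannot be known before the costs are.

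**If the nurse arm does less well than planned**

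- At 8%, the threshold falls to 5.4/3.9 = 1.38. With costs of 100 and 200: N v U = 200/0.054 = 3,704; N v Q = 100/0.015 = 6,667.
- At 7.5%, with costs of 50 and 200: N v U = 200/0.049 = 4,082; N v Q = 150/0.010 = 15,000.
- At 6.5%, with costs of 50 and 200: N v U = 200/0.039 = 5,128, a finite ratio. But the nurse arm costs 150 more than Quitline for no extra quitters, so it is dominated.

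These sums use plain differences in quit rates. A natural quit rate taken equally from every arm would cancel in the differences. A relapse adjustment by one common factor would scale all the ratios alike and leave the thresholds unchanged.

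**The case against.** The best defence is that the head-to-head ICER is planned, because the abstract says so. No section uses the word only or states that it overrides another, and an article may leave the mechanics of an incremental analysis to a fuller document. This stands in part. The document as a whole does not omit the comparison, and ranking rules need not appear in an article. But the comparator is stated here, in five places, and the places disagree. Condensation does not explain that.

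A reader might infer that the economic objective would go unanswered. The documents do not support that. Costs and quit rates are collected in all three arms, and the nurse-versus-Quitline increment follows by subtraction. The two ratios alone do not give it, but the incremental costs and quit rates behind them do. What is missing from the Methods is the commitment to report it.

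A reader might also infer that usual-care ratios flatter the nurse model. That depends on undocumented costs and reverses below a cost ratio of 2.41, as the table shows. Nor would a weak nurse arm be hidden: the Data Analysis section compares cessation across all three arms, and a Quitline ICER is planned too. In the equal-rates case above, readers would see 1,282 for Quitline beside 5,128 for the nurse model. The largest gap shown, 4,082 against 15,000, needs the nurse rate to fall from 12% to 7.5%.

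**Conclusion.** The point holds as an internal contradiction on a primary outcome: the abstract and the hypothesis require nurse versus Quitline, and the economic Methods, the Primary outcomes section and the Background do not include it. Followed alone, the Health economic analysis section would produce no nurse-versus-Quitline ICER.

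The numerical consequence has no fixed size or direction. At the planned rates, across the illustrative costs, the usual-care ratio ranges from well below the head-to-head figure (3,191 against 4,545) to well above it (1,596 against 909). This rests on assumed costs, on the planning quit rates, and on the nurse model being both dearer and more effective than Quitline. Recruitment, data collection and the cessation analysis are unaffected. It should be settled before the results are known, but it is a modest correction.

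**What to change.** Bring the Primary outcomes section, the Health economic analysis section and the Background sentence into line with the abstract and the hypothesis:

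- Keep the two ICERs against usual care, which every section plans.
- Add nurse model versus Quitline referral: incremental cost, incremental quit rate and ICER.
- Present the results as one three-arm incremental analysis, with the arms ordered by cost, and report any dominated or extendedly dominated arm as such. If the nurse arm is dominated by Quitline, give the two increments and say so, rather than print a negative or undefined ratio.

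The cost is a change of wording and one more calculation on data already collected. The one drawback for the investigators is that the nurse model's figure may look less favourable than its ratio against usual care.
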